### Subgroup analyses

Subgroup analyses will be performed for the following subpopulations:

- Age: [50, 60), [60, 70), [70, 75) years
- PSA: [1.5, 3), [3, 4), [4, 10), [10, +inf) ng/mL
- Screen-naïve vs not screen-naïve patients
- Biopsy-naïve vs not biopsy-naïve patients

Statistical tests for effect heterogeneity across subpopulations will be performed by jointly testing the interaction (product) terms in generalised linear models or marginal models (Pepe and Alonzo 2001), as appropriate. No correction for multiple comparisons will be made.

### Additional analyses

Due to updates in the Stockholm3 assay system to reduce measurement errors in the biomarkers included in the Stockholm3 risk prediction model, Stockholm3  $\geq 11\%$  as a selection criterion for randomization may be more sensitive than PSA  $\geq 3$  (i.e. more men with clinically significant prostate cancer will be randomized based on the criterion Stockholm3  $\geq 11\%$  compared with PSA  $\geq 3$ ). If this turns out to be true, we will perform analyses where we “count backwards” (increase the S3M cutoff) and compare biopsy rates at identical sensitivity for clinically significant prostate cancer when comparing diagnostic strategies involving S3M compared with PSA  $\geq 3$  (as described in Grönberg et al.).

We will artificially randomise (2:3) those men who screened negative on both screening tests. By doing this, the totals [d]+[h] and [d']+[h'] will become known, which in turn will allow the estimation of quantities like  $\Pr(\text{ISUP} \geq 2, \text{Stockholm3} \geq 11\% \mid \text{Standard arm})$  (i.e., the probability of ISUP  $\geq 2$  and Stockholm3  $\geq 11\%$  in enrolled men randomised to the standard arm). Contrasts between the two study arms with respect to these quantities will be

---

 Where applicable.

performed using the same methodology described in the section “Contrasts between study arms (unpaired design)”.

We may in additional analyses use regression models to model the DP, TPF, and FPF given covariates. We will employ standard generalised linear models or marginal models (Pepe and Alonzo 2001), as appropriate.

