### Analyses

#### *Data structure*

The table below lays out the general data structure for the STHLM3-MRI trial.

|                     |
|---------------------|
| Standard arm |
|---------------------|

|                          | Endpoint = positive (yes) |                   | Endpoint = negative (no) |                   |
|--------------------------|---------------------------|-------------------|--------------------------|-------------------|
|                          | PSA test positive         | PSA test negative | PSA test positive        | PSA test negative |
| Stockholm3 test positive | a                         | b                 | e                        | f                 |
| Stockholm3 test negative | c                         | [d]               | g                        | [h]               |
| Experimental arm  |                           |                   |                          |                   |
|                          | Endpoint = positive (yes) |                   | Endpoint = negative (no) |                   |
|                          | PSA test positive         | PSA test negative | PSA test positive        | PSA test negative |
| Stockholm3 test positive | a'                        | b'                | e'                       | f'                |
| Stockholm3 test negative | c'                        | [d']              | g'                       | [h']              |

Note: since the study protocol dictates that only those patients who screen positive on either screening test are referred for further work-up, the number of patients reported between brackets are unknown. In a standard screen-positive study, the total number of patients [d]+[h] (and [d']+[h']) is known. However, this study combines a paired and a randomised design and only those men who screen positive on either test are randomised. Therefore, the quantities [d]+[h] and [d']+[h'] are unknown in the present study.

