#### *Updated sample size calculations (performed during Spring and Summer 2019)*

We revised the sample size calculations above in order to have sufficient statistical power to answer comparisons of Stockholm3 vs. PSA within the experimental arm.

The updated, final sample size is the result of a balance between time and financial constraints on one hand and the need to maximise the power for contrasting Strategies 6 vs. 3 on the other hand. In fact, different assumptions about the joint probability of  $ISUP \geq 2$  and screening positive on the PSA test [ $Pr(ISUP \geq 2, PSA \geq 3 \text{ ng/ml})$ ] and about the TPF of the PSA test [ $Pr(PSA \geq 3 \text{ ng/ml} | ISUP \geq 2)$ ] lead to different required sample sizes.

Based on the sample size calculation, we decided to increase the number of men invited into the study to ~50000. Based on an updated estimate of the expected participation rate (25%), this will lead to ~12500 men included in the study and to ~2100 randomised men based on PSA or Stockholm3 (assuming ~16.5% of the enrolled men will test positive on either screening test; 13% passed on PSA alone, leading to ~1600 randomized men with  $PSA \geq 3 \text{ ng/ml}$ ), ~1700 of whom will complete the diagnostic chain, assuming a 20% drop-out rate.

The updated sample size will give:

1. 50–90% power for the contrast S3M+TBx+SBx versus PSA+TBx+SBx. This is based on the following assumptions: 0.015–0.03 probability of detecting  $ISUP \geq 2$  and screening positive on the PSA test (Grönberg et al. 2015), 0.57–0.63 TPF for the PSA test (Thompson et al. 2005),  $rTPF$  (Stockholm3  $\geq 11\%$  vs  $PSA \geq 3$ ) equal to 1 (Grönberg et al. 2015), and a conservative DDR estimate (Alonzo, Pepe, and Moskowitz 2002). The non-inferiority margin was set to  $\delta = -\log(0.78)$  and alpha to 0.025.

Note: the contrast S3M+TBx+SBx versus PSA+TBx+SBx is nested within the experimental study arm, where about 7500 men will be included (due to the 2:3 randomisation). We further assumed a 20% drop-out rate, leading to 6000 men available for the analyses.

| DR_psa | TPR_psa | power |
|--------|---------|-------|
| 0.015  | 0.57    | 0.48  |
| 0.020  | 0.57    | 0.60  |
| 0.025  | 0.57    | 0.70  |
| 0.030  | 0.57    | 0.77  |
| 0.015  | 0.59    | 0.52  |
| 0.020  | 0.59    | 0.64  |
| 0.025  | 0.59    | 0.73  |
| 0.030  | 0.59    | 0.81  |

|       |      |      |
|-------|------|------|
| 0.015 | 0.61 | 0.55 |

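### The artificial 2:3 randomisation of double-negative men adds no information; a fixed calculation estimates the same ratio with a slightly tighter interval

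*Combined protocol and SAP*

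**What the plan says.** The SAP's Data structure section explains that only men positive on PSA or Stockholm3 are randomised, so the double-negative men belong to no arm: "Therefore, the quantities [d]+[h] and [d']+[h'] are unknown in the present study". Under Additional analyses the plan deals with this by chance allocation: "We will artificially randomise (2:3) those men who screened negative on both screening tests". It continues: "By doing this, the totals [d]+[h] and [d']+[h'] will become known". The aim is to estimate joint probabilities among enrolled men, such as having ISUP grade 2 or higher and a positive Stockholm3 test, for each arm. The arms are then compared with the Wald formulas of the section on between-arm (unpaired) contrasts, which treat the arm totals as fixed.

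The Additional analyses section gives no block scheme, seed, number of repetitions or pooling rule. The SAP's Design section describes blocks of five for the real randomisation but does not extend them to this step. The updated sample size section already divides enrolled men without a draw: it places 7,500 of 12,500 in the experimental arm, a fixed 3/5.

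**The concern.** A man negative on both tests is not biopsied, so whichever arm he is assigned to, he adds one to a denominator and nothing to a numerator. The allocation fractions are known by design. Drawing them at random replaces a known quantity with a noisy version of itself, and two analysts using different seeds could report different ratios from the same data.

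What is at stake is modest: the reproducibility of an additional between-arm estimate, and some precision that the choice of denominator gives away.

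**Working it through.** **Inputs** (SAP, Updated sample size calculations). The section states that "this will lead to ~12500 men included in the study and to ~2100 randomised men based on PSA or Stockholm3". The screen-positive share behind this is put at about 16.5%. Taking 16.5% of 12,500 gives about 2,062 randomised men (about 825 standard, 1,237 experimental) and 12,500 − 2,062 = 10,438 double-negative men. The assumed probability of ISUP grade 2 or higher with a positive PSA test is 0.015 to 0.03 among enrolled men.

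**The plan's own figures first.** 12,500 × 3/5 = 7,500, and 7,500 × 0.8 = 6,000, as stated: "We further assumed a 20% drop-out rate, leading to 6000 men available for the analyses". For contrast 6 vs 3, power = Φ(−log 0.78 / SE − 1.96), with SE² = (b+c)/[(a+b)(a+c)], rTPF = 1, a+c = 6,000 × DR and a = (a+c)(2·TPR − 1)/TPR. With DR 0.020 and TPR 0.57: a+c = 120, a = 29.5, b+c = 181, SE = 0.112, power 0.601 against the stated 0.60. All 16 cells of the table agree to within 0.5 percentage points. That calculation rests on the fixed 3/5 share; no draw is involved.

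**Noise from a simple draw.** Each double-negative man is assigned independently with probability 0.4 or 0.6.

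- SD of the standard-arm count = √(10,438 × 0.4 × 0.6) = 50 men.
- SD of the log ratio = 50.05 × (1/5,000 + 1/7,500) = 0.0167.
- 95% of draws multiply the ratio by exp(±1.96 × 0.0167), that is 0.968 to 1.033. Simulation of 200,000 draws agrees.

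With one list of blocks of five, the ratio in the example below varies only from 0.9997 to 1.0003. With a fixed split it does not vary.

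**Against sampling error.** Assume equal detection rates in both arms and all enrolled men counted. The SAP's Wald variance is 1/x_E − 1/N_E + 1/x_S − 1/N_S.

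| Rate | Events (standard, experimental) | Wald SE, log ratio | Draw variance / Wald variance |
|---|---|---|---|
| 0.015 | 75, 112.5 | 0.148 | 1.3% |
| 0.020 | 100, 150 | 0.128 | 1.7% |
| 0.030 | 150, 225 | 0.104 | 2.6% |

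At rate 0.020 and a true ratio of 1, simulated power against 0.78 is 0.490 with a fixed split and 0.490 with a simple draw; type I error is 0.018 and 0.019.

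**Why the draw is unnecessary for ratios.** Let π be the randomised share of enrolled men, the same in both notional arms because allocation is 2:3 throughout. The joint probability among enrolled men is π × (events / randomised men) in each arm, so π cancels:

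ratio = (x_E/n_E) / (x_S/n_S), with n counting all really randomised men in the arm.

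For 100 and 150 events this is (150/1,237)/(100/825) = 1.0004.

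**Effect on the interval**, same events:

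- Enrolled denominators: 1/150 − 1/7,500 + 1/100 − 1/5,000 = 0.01633; SE 0.128; lower limit exp(−1.96 × 0.1278) = 0.778.
- Randomised denominators: 1/150 − 1/1,237 + 1/100 − 1/825 = 0.01465; SE 0.121; lower limit exp(−1.96 × 0.1210) = 0.789.

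The narrower interval is justified. The enrolled-denominator formula treats the number of screen-positive men as varying independently between arms, whereas the real blocked randomisation fixes their ratio. Even with the noise of a simple draw added, the actual SE is √(0.1210² + 0.0167²) = 0.122, below 0.128. In the example, simulated power rises from about 0.49 to 0.54 with type I error still below 0.025.

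**The case against.** A reader might infer that the planned ratios depend on a random seed and that the non-inferiority verdict for Strategy 6 vs 1 could pass or fail by the draw. A worked case makes this tempting: with 100 vs 150 events and a simple draw, the lower limit runs from 0.753 to 0.804 over 95% of draws, 45% of draws clear 0.78, and over repeated trials at that rate two seeds disagree in about 6%. The documents do not support it as a general statement, for these reasons:

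- Seed dependence of any size needs unblocked allocation. The only scheme the SAP describes is blocks of five, so a blocked split is at least as natural a reading.
- The Additional analyses section borrows the estimators and intervals of the between-arm section. It does not link these contrasts to the 0.78 margin, which stands under Primary endpoints; nor does the between-arm section mention the artificial split when it lists 6 vs 1.
- The worked case sits almost on the margin. Keeping 100 standard-arm events, 0.4% of draws clear 0.78 with 144 experimental events and 99.99% do with 160.
- The noise is small beside sampling error, and the Wald interval on enrolled denominators is already wide enough to cover it.

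All of this stands and limits the size of the point. It does not give the draw a purpose: under every reading, a deterministic calculation serves at least as well. It is also fair to say that the two denominators give different estimators of the same quantity, not identical numbers.

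**Conclusion.** The point holds as a minor improvement. The artificial randomisation carries no information and can be avoided. Under simple allocation it adds an SD of about 1.7% to a between-arm ratio whose sampling SE is about 10% to 15%; under blocked or fixed allocation it adds practically nothing. The gain in precision from using really randomised men as denominators is larger than the draw noise: SE 0.121 instead of 0.128 in the example.

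Only the additional enrolled-population contrasts between arms are affected. Within-arm contrasts such as 6 vs 3, which drives the sample size, and contrasts among really randomised men such as 3 vs 1 are not. The figures assume the SAP's planning numbers (12,500 enrolled, 16.5% screen-positive). The event counts are assumptions within its 0.015 to 0.03 range, with a true ratio of 1 and no drop-out.

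**What to change.** Replace the artificial randomisation in the SAP's Additional analyses with a deterministic calculation:

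1. For ratios, divide each strategy's events by all really randomised men in that arm, not only those positive on the test in question, and apply the existing relative-scale Wald formula with those denominators.
2. For absolute rates among enrolled men, add 2/5 and 3/5 of the double-negative total to the standard and experimental denominators, consistent with the 7,500 of 12,500 in the power calculation.

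If the sponsor prefers to keep a random split, one sentence should state that it is blocked, or else give a prespecified seed or say that results are averaged over repeated splits. That would settle reproducibility but would forgo the tighter interval.

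The cost is a few lines of SAP text and code. No data collection or trial procedure changes.

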#### Data Safety Management Board (DSMB)

See protocol.

#### Handling of missing data

Missing data with respect to outcome data (most importantly, participants who are recommended biopsy but never undergo the procedure) will primarily be handled by performing analyses on both the ITT and the PP populations. The analysis on the PP population inherently makes a missing-completely-at-random (MCAR) assumption. However, there is a chance that there is uneven dropout levels in the two arms. For example, men randomized to undergo MRI may to a higher degree choose to undergo biopsy since there is visual feedback of a lesion. If deemed necessary to understand and interpret study results, we may therefore perform multiple imputation based on the Stockholm3 score to impute outcomes for men who drop out of the study before the biopsy is performed. Briefly, if imputation is performed, it will follow the following protocol:

- *Systematic biopsy arm.* The Stockholm3 test, which is calibrated to systematic biopsy outcomes, will be used to impute biopsy outcome on men who did not undergo biopsy (despite a study recommendation to do so) by performing a Bernoulli experiment using the predicted Stockholm3 risk score for ISUP 2 cancer as a parameter. The analysis will be performed on 1000 multiple imputation datasets and summarized.
- *Experimental biopsy arm.* We will, by using data with the STHLM3MRI trial, fit a model to associate Stockholm3 test and PI-RADS score result to TBx outcome (Stockholm3-TBx). Using this model, we will proceed in a similar way as for the control arm. I.e., we will repeatedly impute outcome using Bernoulli experiments with the predictions from the Stockholm3-TBx model as parameter. The analysis will be performed on 1000 multiple imputation datasets and summarized.

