#### ***Biopsy procedure for targeted biopsies***

**PI-RADS≥3:** 3-4 targeted biopsies on marked lesions + systematic biopsies

**Large diffuse lesions or poor image quality:** Systematic biopsies including lesion

**No PI-RADS $\geq$ 3, diffuse lesions and at least acceptable image quality:** No biopsies are performed.

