**Table of additions and clarifications**

| Date       | Type                     | Description                                                                                                                                                                                                                                                                                                      | Ref Protocol |
|------------|--------------------------|------------------------------------------------------------------------------------------------------------------------------------------------------------------------------------------------------------------------------------------------------------------------------------------------------------------|--------------|
| 2019-11-13 | Sample size calculation  | Decided to increase study size. Power calculation based on assumptions: participation rate (DSMB2; 22%), 13% men randomized; 20% men not following protocol; 55% MRI-negative; size increased to enable secondary contrast comparison s3M+MRI/TBx vs PSA+MRI/TBx (Additional Hypotheses 4). See SAP for details. | 13.9         |
| 2020-11-27 | Clarification            | Clarification of wording in hypothesis descriptions.                                                                                                                                                                                                                                                             | 9            |
| 20200108   | Definition, inclusion    | Men creating referral before 2020-01-09 are included in main analysis.                                                                                                                                                                                                                                           | 13.2         |
| 20200108   | Definition, inclusion    | Age is defined as age at referral creation. Men aged 50-74 are included in main analysis                                                                                                                                                                                                                         | 13.2         |

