### Study populations

1. *ITT population* includes all men who:
  - a. signed the written informed consent to participate in the study,
  - b. fulfilled all inclusion criteria and none of the exclusion criteria,
  - c. were randomised to either study arm.

Conditions for excluding patients from the ITT population, based on deviations from the study protocol:

| Randomisation arm | MRI           | No biopsy | SBx only | TBx only | SBx and TBx |
|-------------------|---------------|-----------|----------|----------|-------------|
| Standard arm      | MRI or no MRI | Include   | Include  | Include  | Include     |
| Experimental arm  | MRI or no MRI | Include   | Include  | Include  | Include     |

Randomised allocation and analysis group for ITT analyses:

| Randomisation arm | Test received                           | Analysis group   |
|-------------------|-----------------------------------------|------------------|
| Standard arm      | Systematic biopsy (with or without MRI) | Standard arm     |
| Standard arm      | Targeted biopsy                         | Standard arm     |
| Standard arm      | Systematic biopsy and Targeted biopsy   | Standard arm     |
| Standard arm      | No biopsy / Other                       | Standard arm     |
| Experimental arm  | Systematic biopsy (with or without MRI) | Experimental arm |
| Experimental arm  | Targeted biopsy                         | Experimental arm |

|                  |                                       |                  |
|------------------|---------------------------------------|------------------|
| Experimental arm | Systematic biopsy and Targeted biopsy | Experimental arm |
| Experimental arm | No biopsy / Other                     | Experimental arm |

2. *PP population* includes men who:

- a. are included in the ITT population,
- b. have a valid PSA value and Stockholm3 score,
- c. have a complete systematic pathology report if randomised to standard arm (but no targeted pathology report),
- d. have a complete MRI report if randomised to experimental arm and (i), (ii), or (iii), as appropriate,
  - i. have a complete systematic and a complete targeted pathology report if PIRADS $\geq$ 3,
  - ii. have a complete systematic pathology report if PIRADS $<$ 3 and Stockholm3 $\geq$ 25% (but no targeted pathology report),
  - iii. did not undergo any biopsy if PIRADS $<$ 3 and Stockholm3 $<$ 25%.

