Conditions for excluding patients from the PP population, based on deviations from the study protocol:

| Randomisation arm | Further specifications                     | No biopsy | SBx only | TBx only | SBx and TBx |
|-------------------|--------------------------------------------|-----------|----------|----------|-------------|
| Standard arm      | No MRI                                     | Exclude   | Include  | Exclude  | Exclude     |
| Standard arm      | MRI                                        | Exclude   | Exclude  | Exclude  | Exclude     |
| Experimental arm  | No MRI                                     | Exclude   | Exclude  | Exclude  | Exclude     |
| Experimental arm  | MRI PIRADS $\geq$ 3                        | Exclude   | Exclude  | Exclude  | Include     |
| Experimental arm  | MRI PIRADS $<$ 3 and Stockholm3 $\geq$ 25% | Exclude   | Include  | Exclude  | Exclude     |
| Experimental arm  | MRI PIRADS $<$ 3 and Stockholm3 $<$ 25%    | Include   | Exclude  | Exclude  | Exclude     |

The analyses will be performed and reported on both the ITT and PP population.

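### Between-arm per-protocol contrasts are biased by loss at the biopsy step even when that loss is completely random, because unbiopsied low-risk MRI-negative men stay in the experimental arm while standard-arm non-completers all leave

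*Combined protocol and SAP*

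**What the plan says.** SAP, Study populations, defines the PP set separately by arm. A standard-arm man needs a complete systematic pathology report. An experimental-arm man needs a complete MRI and then:

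- with PI-RADS ≥3, he must "have a complete systematic and a complete targeted pathology report";
- with PI-RADS <3 and Stockholm3 ≥25%, he must have a complete systematic report;
- with PI-RADS <3 and Stockholm3 <25%, he must have had no biopsy.

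The accompanying table is headed "Conditions for excluding patients from the PP population, based on deviations from the study protocol". All analyses are to be reported on both the ITT and PP populations, and neither is named as primary.

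SAP, Handling of missing data, identifies men who are advised to have a biopsy but never have it as the main source of missing outcomes. It says: "The analysis on the PP population inherently makes a missing-completely-at-random (MCAR) assumption". It then warns that drop-out may differ between arms and allows, but does not require, multiple imputation.

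The protocol addendum (section 19) gives the planning figures "20% men not following protocol; 55% MRI-negative". Protocol 13.4, under the biopsy procedure for targeted biopsies, directs "Systematic biopsies including lesion" for large diffuse lesions or poor image quality.

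**The concern.** The SAP treats uneven drop-out as the threat and MCAR as sufficient protection. The arms, however, lose men from different denominators. A standard-arm man without a biopsy leaves, whoever he is. In the experimental arm only men advised to have a biopsy can be lost at that step, so the men who remain are over-weighted with MRI-negatives, who contribute no detections. Equal, purely random loss therefore lowers experimental-arm detection of every grade and its biopsy rate, and leaves the standard arm unchanged.

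The affected contrasts are 3 vs 1 (the primary contrast of Publication 1), 2 vs 1, 9 vs 7, 6 vs 1 and 5 vs 1. For ISUP 1, where a lower rate is the claim, the bias favours the experimental arm. For ISUP ≥2 it works against it and could produce a spurious disagreement between ITT and PP.

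The same table also classes experimental-arm men with systematic biopsy only as deviators, unless they have PI-RADS <3 and Stockholm3 ≥25%. Some of these men may have been managed as protocol 13.4 directs.

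**Working it through.** **Inputs.**
- MRI-negative 55%, so MRI-positive share π = 0.45 (protocol addendum; taken to apply to PSA ≥3 men).
- Loss 20% (addendum; SAP sample size).
- Standard-arm ISUP ≥2 detection 0.18, margin 0.04, one-sided α 0.025 (SAP, original sample size).
- rDP 1.3, and about 1600 randomised men with PSA ≥3 (SAP, updated sample size). At 2:3 allocation this is 640 and 960.
- ISUP 1 rate: an assumption, 0.10 to 0.18. The upper end follows from the remark in protocol 8.2 that about half of cancers found by systematic biopsy are low risk.

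**The plan's own figure.** For 3 vs 1 the SAP states more than 90% power. With 512 and 768 completers and detection of 0.18 and 0.18 × 1.3 = 0.234, the SE is √(0.18×0.82/512 + 0.234×0.766/768) = 0.0228. Power is Φ(0.094/0.0228 − 1.96) = 98.4%, consistent with the SAP.

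**Bias factor.** Let a fraction r of biopsy-recommended men be lost at random after MRI. Detections shrink by (1 − r) and the experimental denominator by (1 − πr):

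E[PP detection, experimental] = true detection × (1 − r)/(1 − πr).

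In the standard arm both shrink by (1 − r), so nothing changes.

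| r | Factor |
|---|---|
| 5% | 0.95/0.9775 = 0.972 |
| 10% | 0.90/0.955 = 0.942 |
| 20% | 0.80/0.91 = 0.879 |

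**Sensitivity of the r = 20% factor.**
- MRI-positive share of 0.35 or 0.60 instead of 0.45: 0.860 or 0.909.
- If 5–20% of MRI-negative men have Stockholm3 ≥25% (assumed), they too are advised to have a biopsy and can be lost. The recommended share becomes 0.4775–0.56, and the factor 0.884–0.901.
- Stage of loss: if 10 points of the 20% go before MRI, the biopsy-stage loss is 1 − 0.80/0.90 = 11.1% and the factor is 0.8889/0.95 = 0.936. If all 20% go before MRI, the factor is 1.

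**Consequences at r = 20%, all after MRI** (512 and 960 × 0.91 = 873.6 men).
- *ISUP ≥2, rDP 1.3.* PP detection is 0.234 × 0.879 = 0.206, so the difference falls from +5.4 to +2.6 points. The SE is 0.0218, and power is Φ(0.0657/0.0218 − 1.96) = 85%.
- *ISUP 1, no true difference.* At a rate of 0.18 the PP experimental rate is 0.158, SE 0.0210, and one-sided error Φ(0.0218/0.0210 − 1.96) = 17.8%. At 0.10 it is 0.088, SE 0.0164, and error 11.1%.
- *Biopsies.* 0.45 × 0.879 = 39.6% instead of 45%, against 100% in the PP standard arm by definition.

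With half the loss before MRI (820.8 experimental men), the same formulas give ISUP 1 error of 5.8–7.8% and ISUP ≥2 power of 94%.

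**What is not affected.**
- Within-arm rTPF, (a+b)/(a+c): random loss scales a, b and c equally, so 6 vs 3 and 5 vs 2 keep their value.
- Enrolled-men denominators (SAP, Additional analyses; 16.5% screen-positive): the between-arm ratio changes by (1 − 0.165×0.2)/(1 − 0.165×0.45×0.2) = 0.967/0.985 = 0.98.
- ITT with equal loss: 0.187/0.144 = 1.30, so the ratio is intact.

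**Systematic-only men.** The documents give no frequency. If they were 2%, 5% or 10% of MRI-positive men (assumed) with average detection, excluding them would give factors of 0.989, 0.972 or 0.942 with no drop-out at all.

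**The case against.** ITT is always reported alongside PP, and its ratio is unbiased under equal drop-out. The SAP discloses its assumption, and its optional imputation for the experimental arm conditions on PI-RADS. The SAP also expects better compliance once a lesion is seen, which argues against a 20% loss among MRI-positive men. All of this stands and limits the impact. It does not replace a valid PP estimate: imputation is discretionary, its standard-arm version is described only for ISUP ≥2, and the warning about uneven drop-out misses the bias that equal drop-out creates.

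Several stronger readings are tempting but not supported:

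- That every PP contrast is biased. The within-arm contrasts, including 6 vs 3, which drives the sample size, are not.
- That any random drop-out causes bias. Loss before MRI that ignores MRI status does not.
- That only MRI-positive men are removed. Unbiopsied PI-RADS <3 men with Stockholm3 ≥25% are too, as are all experimental-arm men without an MRI.
- That PP could yield a false non-inferiority claim. By this route the ISUP ≥2 bias is conservative.
- That the biopsy conclusion is at risk. A shift from 45% to 40% against 100% cannot reverse it.
- That protocol 13.4 shows the systematic-only men belong in PP. Those men were biopsied, so they are not non-completers, and the documents do not say that all of them score PI-RADS ≥3. A scan without a PI-RADS score already fails the complete-MRI definition. Step 5b in protocol 13.10 gives PI-RADS ≥3 men targeted plus systematic biopsies with no such exception. The texts conflict, and the documents do not settle which governs.

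**Conclusion.** The plan is wrong as written on this point. For between-arm PP contrasts among randomised screen-positive men, MCAR at the biopsy step does not give an unbiased comparison. Experimental-arm detection is understated by about 3%, 6% and 12% at biopsy-stage losses of 5%, 10% and 20%. The 12% is the upper end for the plan's 20% figure, because the documents do not say how much is lost before MRI; with half lost there it is about 6%.

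The one exposure to a false claim is PP superiority on ISUP 1. At the upper end its one-sided error is about 11–18% rather than 2.5%. This rests on the assumed 10–18% ISUP 1 rate in both arms; 18% would mean 0.18/0.45 = 40% of MRI-positive men, so the top of that range is demanding. For ISUP ≥2 the cost is power, about 85% rather than 98% at rDP 1.3. The treatment of systematic-only men is a separate inconsistency of unknown size.

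**What to change.** 1. For between-arm PP contrasts, estimate experimental-arm rates of ISUP ≥2, ISUP 1 and biopsy by standardising over three cells: PI-RADS <3 with Stockholm3 <25%; PI-RADS <3 with Stockholm3 ≥25%; PI-RADS ≥3. Weight the rate among protocol completers in each cell by that cell's share of all experimental-arm men with a complete MRI, and use a delta-method or bootstrap interval. In the worked case this returns 0.45 × 0.52 = 0.234, the true value. The experimental-arm variance is 0.52²×0.45×0.55/960 + 0.45²×0.52×0.48/345.6 = 0.000216, so the SE of the difference is 0.0225 against 0.0218 for the crude PP estimate, about 3% wider. Power at rDP 1.3 is Φ(0.094/0.0225 − 1.96), about 99%.
2. Replace the MCAR sentence. State that biopsy-stage loss biases the crude between-arm PP contrast even under MCAR, and that the standardised estimate assumes loss is random within MRI/Stockholm3 cell.
3. Reconcile protocol 13.4 (large diffuse lesions or poor image quality) with Step 5b of protocol 13.10 and with the SAP's PP criteria and table, so that men managed as the agreed protocol text directs are not counted as deviators. Report how many there are.

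The cost is SAP wording, a few lines of code and the slightly wider interval. No new data are needed.
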